### Comparisons

Many Chinese medicine studies set Chinese medicine plus Western medicine as the experimental group and solely modern medicine as the control group. This may lead to bias. Therefore, we will use a placebo control group for comparison.

### Chinese medicine syndrome subgroups

During the follow-up period, the enrolled subjects will be evaluated to determine whether they should be assigned to a subgroup for dampness-heat syndrome, the definition of which will be drawn up according to “The Guiding Principles for Clinical Research of New Chinese Medicines (trial)” in 2002 edited by Zheng Xiaoyu [33]. In the theory of Chinese medicine, the Fuling-Zexie decoction is no longer suitable when patients have dampness-heat syndrome.

### Interventions

Subjects will be given therapeutic agents (Chinese medicine) or a placebo.

The Chinese medicine intervention group will receive a Fuling-Zexie decoction of one dose a day taken orally after a meal. If the subject entered the subgroup after evaluation, the intervention will be switched to a Huangqin-Shengjiang-Banxia decoction until the combined damp-heat syndrome subsides.

For the placebo group (Chinese medicine placebo), the size, appearance, packaging, and administration method will be the same as those of the therapeutic drugs.

During the trial, the investigators will monitor the dietary and exercise conditions of the subjects every day.

### Elimination and termination criteria

The elimination criteria are as follows: (1) serious violation of exclusion standards after enrollment, (2) not completing the experimental drug administration during the experimental period as required after enrollment, and (3) incomplete one-month follow-up and no test records available for evaluation.

The termination criteria are as follows: (1) a gout attack, (2) severe adverse events, (3) condition deteriorated and required urgent medical attention, (4) the researcher recommended test termination because of the safety of the subjects, and (5) people unwilling to continue to participate in this study for personal reasons.

We will keep in touch with the subjects who drop out to observe any subsequent adverse events and collect data.

### Strategies to improve adherence to interventions

The compliance of investigators and subjects is an essential factor in the clinical research process and clinical effects. To ensure compliance, investigators or the designated representative must give detailed information about the clinical trial to the subjects and obtain informed consent after a sufficient and detailed explanation.

The compliance evaluation of the subjects will mainly be judged from the status recorded in the subject’s log card and the questions asked by the researchers.

### Plans to promote participant retention and complete follow-up

First, the investigators will keep in touch with the subjects, and regular telephone follow-ups and reminders for follow-up visits will be implemented. Second, our research system will issue the prescription a day in advance. Third, the subjects will receive free tests. Fourth, transportation subsidies will be given after each follow-up visit to encourage subjects to remain engaged and complete follow-up surveys.

### Outcome measures

#### Primary outcome measure

The reduction of serum uric acid is the primary outcome measure.

#### Secondary outcome measures

The secondary outcome measures are as follows: (1) Chinese syndrome score, measurement of the channels and collaterals, and tongue diagnosis evaluation; (2) glomerular filtration rate, urinary β2 microglobulin, and uric acid excretion fraction; (3) incidence rate of complications, such as gout, hyperlipidemia, cardiovascular events, diabetes, etc.; (4) ultrasound of both ankles and the first metatarsophalangeal joints [34]; (5) evaluation index of metabolites, including blood and urine metabolites; (6) inflammatory index: hsCRP, TNF-a, IL-6, and IL-8; and (7) intestinal microecology (note: this index is tested by a separate participant).

### Security indicators

Security indicators include the following: (1) liver function (alanine aminotransferase ALT, aspartate aminotransferase AST) and renal function (blood urea nitrogen, creatinine); (2) routine blood tests, routine urine tests, routine stool tests + occult blood; and (3) an electrocardiogram and ultrasound of the urinary system.

### Data collection and analysis

Within the 12-week study period, there will be 4 visits: the first at week 0, the second at 4 weeks ± 3 days, the third at 8 weeks ± 3 days, and the fourth at 12 weeks ± 5 days. The data collection and completion of the CRF will be performed by two research assistants who will be blinded to the grouping of the participants. The EPIdata3.1 database software package will be used to establish a database for data entry, and double input data will be used for data entry.

The clinical trial monitors will check the quality of data entry regularly. The database after verification will then be checked by logic inspection, and the outliers will be checked with the original laboratory documents, and the final checked database will be converted into an DATABASE in the format of the SPSS statistical software package and locked for statistical analysis.

### Statistical analysis

All statistical tests will be two-sided, and *α* = 0.05 will be considered statistically significant.

We will use a *t*-test (or Wilcoxon matched-pairs signed-ranks test if the data are non-normally distributed with uneven variances) to compare the decrease in uric acid between two groups.

For secondary outcomes, the *t*-test and Wilcoxon test will be conducted to compare the differences in measurement data (such as index mean, standard deviation, and median) between the groups. Repeated measures analysis of variance will be used to compare multiple measures of the scale and symptom rating among groups. The chi-square test (or Fisher’s exact test) and 3×C table will be utilized to determine the differences in the proportion, frequency, and total effective rate of the indices in the Chinese medicine group and placebo group.

To analyze the influencing factors of curative effects, non-conditional logistic regression analysis will be performed. For missing data from long-term follow-up, the last carry-over method (LOCF) will be used.

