**Methods:**

This pilot study is a prospective, double-blinded, randomized, placebo-controlled clinical trial developed from March 2020 to December 2021. Thirty people with asymptomatic hyperuricemia will be recruited and assigned to either the Chinese medicine group or placebo group, and each group will have 15 subjects. During the 12-week observation period, there will be 4 visits. The decline in uric acid is the main outcome measure, and urinary uric acid, inflammatory biomarkers, and other indices that may be involved in lowering uric acid are the secondary outcome measures.

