### Study design

This is a 12-week, single-center, prospective, double-blinded, randomized, placebo-controlled clinical trial. We used the SPIRIT reporting guidelines to perfect the protocol [32], from March 2020 to December 2021. Thirty individuals with asymptomatic hyperuricemia will be randomly assigned to receive Chinese medicine or a placebo at a 1:1 ratio (Figs. 1 and 2).

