### Randomization and allocation

Adopting simple block group randomization, the allocation ratio will be 1:1. SAS9.2 PROC PLAN will be used to carry out procedure coding and random sequence generation by the methodology team.

The random distribution results will be released through the interactive network response random distribution system for clinical research in Guangdong Provincial Hospital of Chinese Medicine. The random assignment table in the random center will be kept strictly confidential until the end of the study.

After the patients are screened as qualified subjects and have given informed consent, the clinicians apply for the randomization system to obtain the randomization results on the internet. Physicians will execute the results according to random grouping and print and paste them on the corresponding position of the case report form (CRF).

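### The non-normal fallback for the primary outcome is a matched-pairs test, but the two randomised arms are independent and unmatched

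*Protocol article*

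**What the plan says.** The Primary outcome measure section states: "The reduction of serum uric acid is the primary outcome measure". Each subject therefore contributes one change value.

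The Statistical analysis section gives a t-test for this outcome. The alternative, and the purpose stated for both tests, read: "Wilcoxon matched-pairs signed-ranks test if the data are non-normally distributed with uneven variances) to compare the decrease in uric acid between two groups". Tests are two-sided at 0.05. For the secondary outcomes the same section speaks of a Wilcoxon test between the groups without saying which form.

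The design is set out in three places. Study design: "Thirty individuals with asymptomatic hyperuricemia will be randomly assigned to receive Chinese medicine or a placebo at a 1:1 ratio". Randomization and allocation: "Adopting simple block group randomization, the allocation ratio will be 1:1". Abstract, Methods: "each group will have 15 subjects". None of them, nor any other section, describes matching a subject in one arm to a subject in the other.

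**The concern.** The test and the comparison do not fit each other. The signed-rank test works on differences within pairs, whereas a comparison of change values between two unmatched arms is a two-sample problem. An analyst who follows the sentence literally must invent a pairing, and different pairings of the same data give different p-values. The article hands the analysis to a third party, who may well take the named test at its word.

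The trigger adds a smaller difficulty. It asks for non-normality together with uneven variances. Skewed data with similar spread in both arms would therefore not reach the rank test, although that is a usual reason for having one.

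At stake is the between-arm result on the primary outcome whenever the fallback is used. The article intends that outcome to feed the sample size of a larger trial.

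**Working it through.** **What can be reproduced.** The article gives no effect size, standard deviation or power for this trial (the α and β under Sample size belong to the later large trial). There is no stated figure to reproduce. The check is of the test's logic, followed by simulation under assumed distributions.

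**Inputs from the article.** 15 per arm (Abstract, Methods); two-sided α = 0.05 (Statistical analysis); one change value per subject (Primary outcome measure); no matching (Study design; Randomization and allocation); subjects may be removed after enrolment (Elimination and termination criteria). **Assumed:** the distributions and shifts shown below.

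**Step 1, what each test needs.** Let x₁…x₁₅ and y₁…y₁₅ be the changes in the two arms.
- Signed-rank: choose a pairing π, form dᵢ = xᵢ − y_π(i), and sum the ranks of |dᵢ| over positive dᵢ. With 15 against 15 there are 15! ≈ 1.3 × 10¹² possible pairings, and the design selects none of them.
- Rank-sum: U = number of (i, j) with xᵢ > yⱼ, over 15 × 15 = 225 cross-arm comparisons. No pairing enters, and unequal arms are no obstacle (15 against 13 gives 195 comparisons).

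**Step 2, dependence on the pairing.** One simulated data set (lognormal, log-scale SD 1, shift 0.8, 15 per arm) was chosen because its rank-sum p was near 0.05; the value was 0.045. Re-pairing the same 30 values at random 10,000 times gave signed-rank p from 0.003 to 0.60, with median 0.23. Only 3.7% of pairings were below 0.05. This illustrates the problem; it does not estimate how often a conclusion would change.

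**Step 3, type I error and power.** Each entry is the share of 10,000 simulated trials with p < 0.05. The pairing was fixed independently of the outcomes. The Monte Carlo standard error is at most √(0.5 × 0.5 / 10,000) = 0.005.

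| Distribution | Null: signed-rank | Null: rank-sum | Shift | Power: signed-rank | Power: rank-sum |
|---|---|---|---|---|---|
| Lognormal | 0.044 | 0.042 | 1.0 | 0.50 | 0.71 |
| Normal | 0.051 | 0.044 | 1.0 SD | 0.70 | 0.72 |
| t, 3 df | 0.048 | 0.044 | 1.2 | 0.56 | 0.65 |

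The signed-rank test keeps its level. The power loss is about 0.21 for the skewed case (0.71 − 0.50), 0.09 for the heavy-tailed case (0.65 − 0.56) and 0.02 for normal data (0.72 − 0.70).

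**Step 4, unequal arms.** With 15 values in one arm and 13 in the other, pairs cannot be formed one to one, and the software returns an error.

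**The case against.** The strongest reply is that this is a naming slip in a branch that may never be used. The sentence itself says the comparison is between groups, which points to the rank-sum test. The planned first choice is the t-test, and the fallback needs two conditions at once. In a check with Shapiro-Wilk in either arm and Levene's test, both at 0.05, and the same distribution in both arms (normal, t with 5 df, moderately skewed lognormal), the joint condition was met in fewer than 7% of data sets. Those tests and distributions are assumptions; stronger skew or truly different variances would raise the frequency. The reply stands as a limit on the weight of the point. It does not make the written test right, and nothing elsewhere in the article corrects it.

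Several stronger readings are tempting and are not supported:
- *The primary p-value is invalid.* The t-test is untouched, and Step 3 shows a nominal level for the fallback when the pairing is blind to outcomes. Validity would fail if pairs were chosen after seeing the data, which the article does not propose.
- *The test would be run before-after within each arm and so credit the drug with a shared fall.* The sentence assigns it to a between-group comparison.
- *Any drop-out makes it uncomputable.* Last observation carried forward is planned for missing follow-up and may keep a drop-out in the analysis. The difficulty arises when eliminated subjects leave the arms unequal.
- *The t-test wrongly assumes equal variances.* The article does not name the pooled form.
- *The planned 3×C table is wrong for two arms.* The text ("3×C table will be utilized to determine the differences in the proportion, frequency, and total effective rate") does not say that the rows are arms.

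**Conclusion.** The point holds for the fallback test of the primary outcome. A paired test is assigned to two independent, unmatched arms. If used as written, it has three consequences: a p-value that depends on a pairing the design does not define, lost power on skewed data, and no result at all if the arms end unequal.

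The size of the power loss rests on the assumed distributions, since the article gives none. That the test is wrong for the comparison rests on the article's wording alone. This should be fixed, but it is not critical: the branch is conditional, the trial is a pilot, and the error rate is not inflated under outcome-blind pairing.

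**What to change.** In the primary-outcome sentence of Statistical analysis, name the Wilcoxon rank-sum (Mann-Whitney) test for two independent samples, applied to the change in serum uric acid, as the alternative to the t-test. Let non-normality alone trigger it, without the further requirement of uneven variances. The two changes belong together: widening the trigger while leaving the paired test in place would only make the problem more frequent. In the secondary-outcome sentence, add that the Wilcoxon test is the same two-sample test. That wording already fits, so it needs clarifying and not replacing.

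The cost is a phrase in each of two sentences. No data collection, visit or sample size changes. In the simulations above the replacement kept its level (0.042 to 0.044), and it gives one p-value per data set whatever the arm sizes. The change should be recorded before the allocation is opened.

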### Sample size

This study will enroll 30 subjects. Further large-scale RCT trials will estimate the size of the sample according to the results of the main outcome indicators obtained from this study and use the sample content estimation formula to compare the two means to calculate the sample content, *α* = 0.025, *β* = 0.2. The sample size ratio of the test group and control group is 1. The follow-up rate is set according to the pre-experiment follow-up rate.

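### The primary t-test uses week-0 uric acid only by subtraction; ANCOVA at one named visit would usually be more precise at almost no cost

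*Protocol article*

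**What the plan says.** Under Primary outcome measure, the article states: "The reduction of serum uric acid is the primary outcome measure". The Statistical analysis section then names a t-test, with a Wilcoxon test as fallback, "to compare the decrease in uric acid between two groups". It names no covariate for this comparison. Repeated measures analysis of variance is kept for the scale and symptom ratings, and logistic regression for factors that influence the curative effect. The significance rule is "All statistical tests will be two-sided, and *α* = 0.05 will be considered statistically significant".

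The Data collection and analysis section sets the schedule: "there will be 4 visits: the first at week 0, the second at 4 weeks ± 3 days", with further visits at weeks 8 and 12. The week-0 value is therefore available, and there are three later visits at which a decrease could be formed. None of the three is named as the primary one.

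On size, the Sample size section says "This study will enroll 30 subjects", and the Study design section sets 1:1 allocation, so 15 per group. No effect size, SD or power is given for this trial. The same section says that its main outcome results will be used to size a later, larger trial.

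**The concern.** A decrease equals the week-0 value minus the follow-up value. A t-test on it assumes that a subject who starts one unit higher would, without treatment, also end one unit higher. With a correlation below 1 and similar SDs at the two times, the true slope is below 1. Subjects with high starting values then tend to fall more, whichever treatment they receive. Two things follow for the comparison of the arms:

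- The variance of the estimated effect is larger than it would be if the slope were estimated from the data.
- If one arm happens to start higher, part of that difference stays in the estimate.

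Both matter more with 15 per arm than in a large trial. The results are also meant to feed the planning of the next trial, so a wider interval carries forward. The unnamed visit is a supporting point: as written, the primary decrease could be taken at week 4, 8 or 12.

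**Working it through.** **Inputs from the article.** N = 30, 15 per group (Sample size, Study design); two-sided alpha 0.05 (Statistical analysis); visits at weeks 0, 4, 8 and 12 (Data collection and analysis). There is no planning calculation to reproduce, because N = 30 is stated without an effect size, SD or power. For orientation only: with 15 per group, the two-sample t-test has 80% power for a difference of about 1.06 SD of the change.

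**Assumptions, not in the article.** Equal SD s of uric acid at baseline and follow-up; baseline–follow-up correlation rho between 0.3 and 0.9.

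**Step 1: variance per subject.**
- Change score: 2s²(1 − rho).
- ANCOVA: s²(1 − rho²).
- Ratio ANCOVA/change: (1 + rho)/2.

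**Step 2: small-sample cost.** Estimating the slope at N = 30 multiplies the ANCOVA variance by 1 + 1/(N − 4) = 1 + 1/26 = 1.038, and leaves 27 instead of 28 degrees of freedom. Example at rho = 0.5: 0.75 × 1.038 = 0.78, and 30/0.779 = 38.5, so about 39 subjects.

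| rho (assumed) | variance ratio at N = 30 | subjects the t-test needs to match ANCOVA with 30 | 95% CI narrower by | power, t-test → ANCOVA, for an assumed effect of 0.75 SD of uric acid |
|---|---|---|---|---|
| 0.3 | 0.68 | 44 | 18% | 39% → 53% |
| 0.5 | 0.78 | 39 | 12% | 51% → 61% |
| 0.7 | 0.88 | 34 | 6% | 73% → 78% |
| 0.9 | 0.99 | 30 | 0.5% | 99% → 99% |

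The variances break even where (1 + rho)/2 × 27/26 = 1, that is, rho = 52/27 − 1 = 0.93. At rho = 0.95 the ratio is 0.975 × 1.038 = 1.01, so ANCOVA is marginally worse.

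**Step 3: simulation check.** With 20,000 runs per setting, the empirical variance ratios were about 0.68, 0.78, 0.88 and 0.99, in line with the formula. Type I error was about 5% for both methods.

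**Step 4: chance imbalance.** The SD of the baseline difference between arms is s√(2/15) = 0.365s. The probability that it exceeds 0.5 SD in either direction is 2(1 − Φ(0.5/0.365)) = 0.17. Given an imbalance of 0.5 SD, the change-score estimate is shifted by (1 − rho) × 0.5 SD: 0.35, 0.25, 0.15 and 0.05 SD at rho 0.3, 0.5, 0.7 and 0.9. ANCOVA adjusts for this.

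**Step 5: the unnamed visit.** Suppose the best of three visits were picked after seeing the data. With no treatment effect, 15 per arm and equal correlations between the three decreases, the simulated type I error is about 0.13 at a correlation of 0.5 and 0.10 at 0.8, against 0.05 for one visit fixed in advance.

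**The case against.** The strongest reply is that nothing in the plan is wrong. Under randomisation the t-test on the decrease is unbiased and holds its 5% level. Regression to the mean acts on both arms alike. This stands: the point concerns efficiency, not validity.

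Four stronger readings are tempting, and the article does not support them.

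- A reader might infer that the plan ignores baseline. It does not, because a decrease cannot be formed without the starting value.
- A reader might infer that a baseline imbalance passes in full into the result, or that a large one is likely. Only the share (1 − rho) passes through, and the chance of an imbalance above 0.5 SD is about 17%.
- A reader might infer that the trial loses a planned power. It has no power target. The figures in "compare the two means to calculate the sample content, *α* = 0.025, *β* = 0.2" belong to the later trial.
- A reader might infer an inflated error rate of 0.10 to 0.13. That rate would arise only if someone chose the visit after seeing the data, and the article plans no such choice.

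It can also be said that the later trial, if it compares mean decreases, needs the SD of change, which this pilot can report whatever its primary test. That is correct, and the fix includes it. Lastly, the article condenses a fuller protocol, and week 12 is the obvious endpoint of a 12-week trial, so that protocol may name it. That softens the visit point. It does not alter the primary test, which the article itself fixes without adjustment.

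**Conclusion.** The point holds as a nearly free improvement in precision. The planned t-test is valid but forces the baseline slope to 1. Adjusting for week-0 uric acid would cut the variance of the treatment comparison by about 32%, 22% and 12% at rho 0.3, 0.5 and 0.7, and by about 1% at 0.9. It would also remove the part of a chance baseline imbalance that the change score leaves in.

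The size rests on an assumed rho and on equal SDs, neither of which the article gives. If rho is near 0.9 there is almost nothing to gain, and above about 0.93 there is a negligible loss. The practical stake is a wider interval and a less precise estimate for planning the next trial, not an invalid result. The unnamed visit is a real gap in the article but a secondary one, and its error-rate cost is conditional.

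**What to change.** - Make the primary analysis an ANCOVA of serum uric acid at one named visit, with treatment and week-0 uric acid as terms. Week 12, the end of the 12-week period, is the natural choice.
- Report the adjusted difference between groups with its 95% CI.
- Treat weeks 4 and 8 as secondary.
- Report the SD of change and the correlation between week-0 and follow-up uric acid, so that the later trial can be sized for either form of analysis.

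The cost is a change of wording and one degree of freedom, with a negligible loss of precision if rho exceeds about 0.9. No extra visits, samples or subjects are needed. Naming the visit before unblinding also removes any possibility of choosing among three visits after seeing the data.

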## Methods and design

### Study objective

The objectives of the experiment are to study the efficacy and safety data of Chinese medicine therapy for dampness syndrome for hyperuricemia and to screen possible related small molecules/microbial material bases.

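### The factor analysis puts a continuous outcome into a binary model on 30 subjects, and one unqualified 0.05 rule covers a molecular and microbial screen

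*Protocol article*

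**What the plan says.** All places are in the protocol article.

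- **Factor model (Statistical analysis):** "To analyze the influencing factors of curative effects, non-conditional logistic regression analysis will be performed". The article gives no binary response, no list of factors and no limit on their number.
- **Outcome (Primary outcome measure):** the reduction in serum uric acid, a continuous quantity. Secondary outcome measures lists no uric acid responder endpoint. A total effective rate is mentioned once, in Statistical analysis, without a definition.
- **Size:** "This study will enroll 30 subjects" (Sample size), and "each group will have 15 subjects" (Abstract, Methods).
- **Error rule (Statistical analysis):** "All statistical tests will be two-sided", and a level of "0.05 will be considered statistically significant". Secondary or exploratory tests are not exempted.
- **Screen:** one study objective is "to screen possible related small molecules/microbial material bases". Secondary outcome measures includes "evaluation index of metabolites, including blood and urine metabolites" and intestinal microecology.

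**The concern.** There are two linked problems, and both lie in what the plan states.

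First, the model does not fit the main outcome. To run it, the analyst must either cut uric acid reduction into responders and non-responders or use a response that the article leaves undefined. Either way the information available is governed by the smaller response class, which is small in a trial of 30.

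Second, a single 0.05 threshold for all tests is a reasonable rule for one primary comparison. It is not a sound rule for naming targets from a screen, where the number of chance crossings grows with the number of features examined.

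The trial is a pilot meant to support larger studies, and its Abstract says it should help show which target matters. An unstable odds ratio or a nominal p-value read as an identified driver or target would misdirect that work.

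**Working it through.** **Inputs from the article.** N = 30, 15 per arm, "the allocation ratio will be 1:1", two-sided 0.05 for all tests. There is no derivation of N to reproduce beyond 30/2 = 15. The alpha and beta under Sample size belong to a later large trial.

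**Assumed inputs.** Response rate, number of factors k, number of features m, standardised effect d and share of truly changed features π. None is in the article, so ranges are shown.

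**1. Events per factor** = min(responders, non-responders) / k.

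| Response rate | Smaller class | k = 1 | k = 3 | k = 5 | k = 8 |
|---|---|---|---|---|---|
| 50% (best case) | 15 | 15 | 5 | 3 | 1.9 |
| 30% | 9 | 9 | 3 | 1.8 | 1.1 |

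By the common guide of 10 events per factor, 30 subjects support one factor at a 50% response rate (15/10 = 1.5) and fewer than one at 30% (9/10 = 0.9).

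**2. Behaviour of the logistic model with no true factor.** Simulation with n = 30, 50% response, independent standard normal factors and 1,000 runs per setting:

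| k | Median largest spurious odds ratio per SD | Any Wald p < 0.05 | Expected from independent 5% tests, 1 − 0.95^k | Likelihood-ratio error per factor |
|---|---|---|---|---|
| 3 | 1.8 | 11–13% | 14% | 0.08 |
| 5 | 2.1 | 17–20% | 23% | 0.08 |
| 8 | 3.0–3.2 | 30–32% | 34% | 0.12 |

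Ranges span repeated sets of runs. Wald error per factor stays at or below about 0.05. Separation (no finite estimate) is rare up to 5 factors. With 10 factors it occurs in about 5% of runs at a 50% response rate and 15% at 30%. The model's weakness is therefore imprecision: odds ratios of 2 to 3 per SD arise from nothing.

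**3. Cost of dichotomising.** A median split of a normal outcome has relative efficiency 2/π = 2/3.1416 = 0.64 (here π is the circle constant). The article does not say that a median split would be used. This is an illustration.

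**4. Screen at 0.05.** Expected false hits if no feature changes = 0.05 × m.

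| m (assumed) | Expected false hits | Chance of at least one, 1 − 0.95^m, if independent |
|---|---|---|
| 20 | 1 | 64% |
| 100 | 5 | 99.4% |
| 1,000 | 50 | about 100% |

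**5. What share of hits would be false?** Share = 0.05(1 − π) / [0.05(1 − π) + power × π]. Power at 15 versus 15 from the noncentral t is 26% (d = 0.5), 56% (d = 0.8) and 75% (d = 1.0).

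- π = 5%, d = 0.5: 0.0475 / (0.0475 + 0.0131) = 78%. At d = 0.8 the share is 63%.
- π = 20%, d = 0.5: 0.0400 / (0.0400 + 0.0524) = 43%. At d = 0.8 it is 26%.
- The share passes one half only when π < 0.05 / (0.05 + power), which is about 16% (d = 0.5), 8% (d = 0.8) or 6% (d = 1.0).

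**The case against.** The strongest reply is that this is a declared pilot whose authors admit its small size, that a condensed article leaves the response definition, the factor list and false-discovery methods to a fuller plan, and that the next trial is to be sized on the main outcome and not on screened targets. Much of this stands. The absence of those details is no finding, and the article does not say that screened features will determine the next trial. But a fuller plan cannot raise the smaller response class above 15, and the 0.05 sentence is written for all tests. The pilot label does not alter either choice.

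Four stronger readings are tempting and are not supported:

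- **That most leads will be false.** This depends on feature count, effect size and share of true changes, none of which is given. Step 5 shows shares from 26% to 78% under plausible assumptions.
- **That logistic regression inflates false positives.** The any-positive rates in step 2 lie below what independent 5% tests would give, so they reflect the number of looks. The likelihood-ratio test does drift above 0.05, but the main weakness is imprecision.
- **That the unconditional form is the fault.** The trial is unmatched, so that form is appropriate.
- **That every metabolite and microbe will be tested at 0.05.** No feature-by-feature analysis is described, and a note under Secondary outcome measures leaves it unclear whether microbiome samples come from the randomised subjects. The inference rests on the sentence about all tests.

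It is also fair to say that single-factor linear models involve several looks too. That is why they should be reported as estimates and not as significance claims.

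**Conclusion.** The point holds in a limited form. The factor analysis is a poor match to a continuous outcome in 30 subjects: at best 15 events, hence at most 5 events per factor with three factors and 3 with five, with a loss of about 36% of the information if a median split is used. The unqualified 0.05 rule is not a sound basis for naming targets from a screen: about 5 chance hits per 100 features if none truly changes. The bound of 15 follows from the article alone. The number of factors, the response rate, the feature count and the median split are assumptions. The document does not allow a statement of how many leads would be false. The primary comparison of uric acid is not affected.

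**What to change.** 1. Replace the logistic model with linear regression of week-12 serum uric acid on treatment, baseline uric acid and one pre-specified baseline factor at a time. With all 30 subjects this leaves 30 − 4 = 26 residual degrees of freedom and needs no cut-point. Report estimates with confidence intervals. Treat any treatment-by-factor interaction as exploratory only.
2. For metabolite features, and for microbiome features if they come from randomised subjects, flag hits on the between-arm contrast by Benjamini-Hochberg within each family, at a false discovery rate fixed in advance (10% is one workable choice).
3. Restrict the two-sided 0.05 significance claim to the primary outcome, and label the factor and screening analyses hypothesis-generating.

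The cost is a few sentences and minor programming, with no extra data. The real downside is that fewer features will be flagged, and with 15 per arm (56% power at d = 0.8 even at an unadjusted 0.05) some true leads may be missed. Reporting all estimates with intervals alongside the flagged list softens that loss.
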